#### Plain radiography of the feet and hands

Digital radiographs of both feet, ankles and hands will be obtained for all participants. Weight-bearing dorso-plantar and lateral views of each foot will be obtained according to a defined protocol [24] and stored on disc. The participant will stand in a relaxed position with the weight of the participant's body distributed equally. A relaxed position will be achieved by asking the participant to walk on the spot for a few steps and then stand relaxed. For the dorso-plantar view the participant will stand with the plantar aspect of both feet on the detector. The x-ray tube will be angled 15° cranially with a vertical central ray centred at the base of the third metatarsal [24]. For lateral projections the participant will stand on a low platform with the detector positioned at the side of the participant's foot. The x-ray tube will be angled at 90° with a horizontal central ray centred on the base on the base of the first metatarsal [24]. Weight-bearing antero-posterior views of both ankle joints will also be obtained with the participant standing on the low platform. The detector will be positioned behind the participant. The x-ray tube will be angled 90° with a horizontal central ray centred midway between the malleoli [45]. Dorso-palmar views of both hands are to be performed. The palmar aspect of the hand will be placed on the detector with the fingers extended, separated slightly and spaced evenly [31]. A vertical central ray will be centred on the head of the third metacarpal [45]. Each foot, ankle and hand will be imaged separately and the film focus distance will be set at 110 cm for all projections. X-rays will take approximately 20 minutes to complete for each participant.

#### Ultrasound of the plantar fascia

The ultrasound examination will be performed using a variable frequency 8-13 MHz linear transducer with a Logiq-e ultrasound system (GE Healthcare). The participant will be positioned in a self-selected half-lying position, or sitting position if the half-lying position cannot be assumed by the participant, on a couch with their feet hanging over the end of the couch and ankles dorsiflexed to 90 degrees. Real-time sagittal (longitudinal) imaging of the plantar aponeurosis will be performed with the focus adjusted to the depth of the fascia for each participant. Plantar fascia thickness will be measured at a standard reference point where the plantar fascia crosses the anterior aspect of the inferior border of the calcaneus on the longitudinal view but at its thickest point in the transverse plane [46]. Three measurements will be taken and recorded on a paper proforma. The Research Assessor performing the ultrasound will be blind to the results of the clinical assessment. The scan will take approximately 10 minutes for each participant.

Ultrasound images will be retained and digitally stored at the Research Centre for quality control purposes. Consent will be sought in the clinic consent process for the use of anonymised images for educational purposes and in presentations.

#### Clinical interview and physical examination

Participants will be interviewed and examined by a trained Research Assessor who will be blind to the radiographic and sonographic findings. This procedure will comprise three components. Firstly, a standardised clinical interview will be conducted to gather quantitative data relating to foot pain and symptoms in older adults [47], causal and diagnostic attribution, previous injury or surgery, and planned treatment (Table 2). Secondly, a detailed, standardised, examination of both feet will be conducted. This will include assessment of skin lesions; common deformities; foot posture including static arch index [48,49], Foot Posture Index [50], foot length [51], navicular height [49,51]; and range of movement of subtalar inversion and eversion [52], ankle dorsiflexion [53], and 1^st ^MTPJ dorsiflexion [54] (Table 2). Thirdly, a brief standardised physical examination of both hands, and both knees will be conducted (Table 2). This will include assessment of presence of deformity, enlargement, swelling and nodes in both hands [55]; maximal power and pinch grip strength using a Jamar dynamometer and B&L pinch gauge respectively [56]; and presence of varus and valgus deformities at the both knees. Lower extremity physical performance will be also assessed [57].

Plantar pressures from both feet will be recorded during level barefoot walking using a pressure platform (RS Scan^® ^International, Olen, Belgium). This system consists of a 12 mm thick floor mat (578 mm × 418 mm) incorporating 4096 resistive sensors sampling at a rate of 300 Hz. The two-step gait initiation protocol will be used whereby the participant is positioned two step lengths from the front edge of the pressure platform and is instructed to walk in a normal manner, striking the sensor area with the second step [58]. The system will be calibrated at the beginning of each session and recalibrated for participants' individual weight and shoe size prior to each assessment. The participant will complete several practice trials, to allow them to familiarise themselves with the two step approach and calculate their starting position. Three trials will be recorded for each foot. Maximum force (N), peak pressure (N/cm^2^) and contact time (ms) will be collected. Footprints obtained will be divided into masks corresponding to the major structural regions of the foot.

Pre-defined protocols for all components of the interview and assessment will be used for standardisation between Research Assessors. Assessment findings will be recorded on a standard form that is to be checked for missing data immediately post-assessment by the Clinic Co-ordinator or Clinic Support Worker. Discussion between Research Assessors and participants about diagnosis and/or appropriate management will be discouraged. Participants will be advised to discuss clinical queries with their General Practitioner. The interview and assessment will take approximately 40 minutes to complete for each participant.

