#### Mandatory notification of clinical 'red flags'

All participants will be routinely screened during the clinical assessment for signs and symptoms suggesting potentially serious pathology requiring urgent medical attention (Table 2). These are: recent trauma to the feet or hands that may have resulted in significant tissue damage; recent sudden worsening of foot or hand symptoms; and acutely hot, swollen, painful feet or hands [68]. In the event of such findings, participants will be informed that they require urgent attention, a standard fax will be immediately sent to the General Practice, and appropriate medical attention arranged the same day. A letter of confirmation will be subsequently sent to the participants' General Practice.

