#### Mandatory notification of radiographic 'red flags'

In the event of any radiographic red flags (including suspected malignancy, unresolved fracture, infection) reported by the Consultant Radiologist a standard fax will be sent with a copy of the x-ray report to the General Practice notifying them of this. This will subsequently be confirmed by letter.

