#### Discretionary notification of other significant radiographic abnormality

At the discretion of the Consultant Rheumatologist, the General Practice will be notified of other significant radiographic abnormality (e.g. previous fracture, inflammatory arthropathy).

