### Phase 3: Review of general practice medical records

All participants in Phase 1 who give permission for their GP records to be accessed will have their computerised medical records tagged by a member of the Research Centre's Health Informatics Specialist team. All consultations for the 18-month period prior to clinic attendance, and for the three-year period following clinic attendance, will be identified. The four practices participating in this study are fully computerised and undergo annual audits completed by the Health Informatics team to assess the quality and completeness of the data entry at the practices [71].

This data will cover consultations, prescriptions, and referrals. All relevant foot-related consultations will be identified using search techniques based on Read codes and free text entries, which have been previously developed and successfully applied by the Research Centre [28,72]. Participants with a relevant recorded consultation will be classified into those receiving an OA diagnosis recorded by their GP and those receiving non-specific symptom codes (e.g. arthralgia). In addition, all comorbid consultations will be identified and sub-grouped by Read code chapter.

Patterns of primary and secondary health care utilisation will be compared between Phase 2 participants and Phase 1 participants who did not attend the research clinic. All sensitive data (name, contact details) will be removed from the medical records data and the consultation data will be linked to the survey and clinical assessment data by unique survey identifier.

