#### Describing self-care and primary care

Annual consultation rates and cumulative consultation probabilities will be calculated over the three-year period. Using logistic regression and survival analysis techniques, we will investigate further how different phenotypes relate to subsequent patterns of primary care consultation (for joint pain, other morbidities, and specifically for OA) and referral to secondary care. Self-care reported by participants in the surveys at each 18 month time-point will be described.

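### Follow-up for GP consultation starts at a clinic visit that can itself generate GP contacts, in attenders only, and the analysis does not separate those contacts

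*Protocol article*

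**What the plan says.** Under Clinical interview and physical examination, attenders are given a route for questions: "Participants will be advised to discuss clinical queries with their General Practitioner". The preceding sentence limits what the visit itself conveys: "Discussion between Research Assessors and participants about diagnosis and/or appropriate management will be discouraged". Under Communication with participants' general practice, findings go to participants and practices only in specific circumstances.

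Those circumstances are then listed:
- For clinical red flags, "a standard fax will be immediately sent to the General Practice, and appropriate medical attention arranged the same day".
- For radiographic red flags, "a standard fax will be sent with a copy of the x-ray report to the General Practice notifying them of this".
- Other significant radiographic abnormality may be notified to the practice at the rheumatologist's discretion.

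Under Phase 3, consultations are extracted for 18 months before the clinic, and those "for the three-year period following clinic attendance, will be identified". The same section says that health care use "will be compared between Phase 2 participants and Phase 1 participants who did not attend the research clinic". Under Describing self-care and primary care, "Annual consultation rates and cumulative consultation probabilities will be calculated over the three-year period", and logistic and survival models relate phenotype to later consultation and referral. The section on presentation and diagnosis also models consultation on phenotype. Modelling the outcomes of care uses recorded consultations and referrals as the care whose effect is estimated.

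None of these sections distinguishes a contact that the study set in motion from one that the participant sought unprompted.

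**The concern.** The date that opens follow-up is also the date on which the study can prompt a contact. Three results are exposed.

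1. **Rates and cumulative probabilities.** Study-generated contacts are added to ordinary care-seeking in Phase 2 participants.
2. **Attenders against non-attenders.** Only attenders receive the advice and the notifications. Non-attenders also have no clinic date, so the window as described has no defined start for them.
3. **Phenotype and consultation.** Radiographic notifications depend on the x-ray, which also contributes to the phenotype. The prompt may therefore differ between the groups being compared.

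This goes beyond detail that an article leaves to a fuller document. The article itself fixes the window, the outcome and the comparison, and following them as written counts these contacts as natural consultation.

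**Working it through.** **The plan's own figure.** The article computes only a sample size, and that is for functional outcome, not consultation. Take p1 = 0.20, p2 = 0.20 × 1.62 = 0.324, 80% power and 5% significance, assuming a two-sided test and equal groups. The pooled formula gives 197 per group (394 in total) without continuity correction, and 213 per group (426) with it. The second matches the stated 426, and 426 + 80 = 506 recruited. The present point does not affect this figure.

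**Inputs for the consultation check.**
- Background b: the Background section reports that about 80% of people with musculoskeletal foot problems do not consult over three years, so b is about 0.20. This is unrelated to the 20% functional-outcome risk in the sample size.
- Prompted share f: the proportion of would-be non-consulters who consult because of the visit. The documents do not give it. Values of 2%, 5% and 10% are assumed.
- Recruited number: 506, from Sample size.

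**Formulae.** Observed probability P = b + (1 − b) × f. The ratio to an unprompted group with the same true risk is P / b. The study-generated share of consulters is (P − b) / P. The extra consulters number 506 × (P − b).

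| f (assumed) | P with b = 0.20 | Ratio | Study-generated share | Extra among 506 |
|---|---|---|---|---|
| 2% | 0.20 + 0.80 × 0.02 = 0.216 | 1.08 | 7% | about 8 |
| 5% | 0.20 + 0.80 × 0.05 = 0.240 | 1.20 | 17% | about 20 |
| 10% | 0.20 + 0.80 × 0.10 = 0.280 | 1.40 | 29% | about 40 |

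**Sensitivity to the background.** The 20% comes from a cited study, not from clinic volunteers. If b were 0.40 (assumed), P would be 0.412, 0.430 and 0.460, with ratios of 1.03, 1.08 and 1.15.

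**Direction for phenotype ratios** (all values assumed).
- Uniform prompt of 5% with true risks of 10% and 30%: 0.10 + 0.90 × 0.05 = 0.145 and 0.30 + 0.70 × 0.05 = 0.335. The ratio falls from 3.0 to 2.3, towards the null.
- No true difference (b = 0.20) with prompts of 2% and 10%: 0.280 / 0.216 = 1.30, a spurious association. With 2% and 5% it is 0.240 / 0.216 = 1.11.

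The sign of the bias therefore depends on how the prompt varies with phenotype, which the documents do not tell us.

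**The case against.** The strongest objection is that the prompt is weak. The advice redirects people who already have a query. It follows an instruction that discourages discussion of diagnosis and management, and results are mostly withheld. Clinical red flags cover recent trauma, sudden worsening and acutely hot, swollen, painful feet or hands, and many such people would plausibly seek care anyway. Same-day medical attention need not be a GP consultation. All of this stands, and it is why the effect is probably modest. It does not make the effect zero or equal between attenders and non-attenders.

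A second objection is that the attender comparison has no stated causal purpose, and that non-attenders include people without foot pain, so the groups differ in need anyway. This also stands. A study-generated component and an undefined start date still add a difference that is avoidable.

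Three stronger readings are tempting but not supported:
- A reader might infer that the clinic tells every attender to consult. The text concerns those with clinical queries.
- A reader might infer that the visit manufactures the link between phenotype and consultation. A uniform prompt weakens a true ratio, and only a prompt that is stronger in worse phenotypes would create or exaggerate one.
- A reader might infer that study-prompted contacts should be removed from the care models. Those models concern care received, and a prompted consultation is real care. Removing it would code treated people as untreated.

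**Conclusion.** The point holds as a modest source of bias in the consultation outcomes. As written, study-generated contacts enter the three-year rates, the cumulative probabilities, the phenotype models and one side of the attender comparison. That comparison also lacks a start date for non-attenders.

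The documents do not allow the size to be estimated. The ratios of 1.08 to 1.40 rest on a background of 20% and an assumed prompted share of 2% to 10%. They shrink to 1.03 to 1.15 if the background is 40%. At a share of 2% or less the effect is small. For phenotype ratios, neither size nor direction can be claimed. The sample size is unaffected.

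**What to change.** Leave the advice to participants and all safety notifications exactly as they are. The changes below are to recording and analysis only.

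1. **Phase 3 and the two consultation analyses** (presentation and diagnosis; self-care and primary care). Record each study notification, flag contacts that follow one, and report consultation outcomes with and without them. The article prescribes faxes and confirming letters but no log linked to the analysis data, so this needs to be stated.
2. **Early-period sensitivity analysis.** The flag cannot identify contacts prompted only by the advice. Repeat the consultation analyses omitting a pre-specified early post-clinic period, keeping the full window as the main analysis. Show the 18-month pre-clinic rate, which is already extracted, as a reference. It is imperfect, because participants were selected for foot pain in the past year.
3. **Attender comparison.** Use one index date available to both groups, such as the baseline survey date. This gives both groups a defined start. It does not remove the prompt, so the with-and-without reporting applies here too.
4. **Modelling the outcomes of care.** Keep study-prompted contacts as care received, and use the flag only for a sensitivity analysis.

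The cost is a small amount of extra record coding and analysis. The sensitivity analyses will also exclude some genuine contacts, including some that would have happened anyway, which is why they should not replace the main analysis.

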#### Simple anthropometric measurements

Weight (in kg) and height (in cm) of each participant will be measured using calibrated digital scales (Seca Ltd., Birmingham, UK) and a wall-mounted measure (Seca Ltd., Birmingham, UK) respectively.

#### Self-complete clinic questionnaire

During the clinic visit, participants will complete a self-complete questionnaire. The questionnaire will be divided into four main sections: (A) Foot pain; (B) Hand pain and problems; (C) Hip pain; and (D) Knee pain. Questions will relate to pain [40,55,59-63], site-specific function [62,64-66], and GP consultation (Table 2). Section A will be completed by all clinic-attenders. Sections B, C, and D will be completed only by those who reported hand, hip or knee pain respectively in their Health Survey questionnaire. The Clinic Co-ordinator or Clinic Support Worker will guide participants as to which sections need to be completed and will check all questionnaires following completion for any missing data. The questionnaire will take approximately 30 minutes to complete.

Travelling and out-of-pocket expenses will be reimbursed after the assessment.

#### Post-clinic procedure

The digital cameras, study laptop and all completed clinical assessment documentation and questionnaires will be returned to the Research Centre. Digital images will be downloaded from the memory cards and laptop onto a secure server.

A clinical report on the x-ray images will be provided by a Consultant Radiologist at the NHS Trust Hospital. The images and report will be forwarded to the Research Centre where they will be screened by a Consultant Rheumatologist for any radiographic "red flags" or significant radiographic abnormality (see below).

Standardised coding of radiographic features on the foot and hand x-ray images will be carried out by the Research Radiographer (a trained observer with a background in diagnostic radiography). The Research Radiographer will be blinded to all assessment data and the radiologist's report. Foot images will be scored for individual radiographic features, including osteophytes and joint space width, at the 1^st ^MTPJ, 1^st ^and 2^nd ^CMJs, NCJ and TNJ according to the Menz atlas and classification system [24]. With the exception of the TNJ, both dorso-plantar and lateral projections will be used to assess osteophyte and joint space width. For the grading of TNJ osteophytes, only the lateral projection will be used as the dorsal aspect of the joint, where osteophytes most commonly develop, is not easily visualised on the dorso-plantar projection. Standardised coding of radiographic features using the Kellgren and Lawrence grading system will be completed for the ankle joints and sixteen joints in each hand and wrist [67]: the distal interphalangeal joints (DIP), the proximal interphalangeal joints (PIP), the interphalangeal joint of the thumb (IP), the metacarpophalangeal joints (MCP), the thumb carpometacarpal joint (CMC) and the trapezioscaphoid joint (TS).

Consent forms, assessment documentation, digital x-ray images and reports are to be placed in separate secure storage.

#### Communication with participants' general practice

Assessment findings will be communicated to participants and their General Practice only in specific circumstances that will be explained to participants at the start of the clinic:

#### Mandatory notification of clinical 'red flags'

All participants will be routinely screened during the clinical assessment for signs and symptoms suggesting potentially serious pathology requiring urgent medical attention (Table 2). These are: recent trauma to the feet or hands that may have resulted in significant tissue damage; recent sudden worsening of foot or hand symptoms; and acutely hot, swollen, painful feet or hands [68]. In the event of such findings, participants will be informed that they require urgent attention, a standard fax will be immediately sent to the General Practice, and appropriate medical attention arranged the same day. A letter of confirmation will be subsequently sent to the participants' General Practice.

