**Clinical Interview**		
Pre-assessment screening:		
Screen for clinical "red flags"	Recent significant foot or hand injury Recent sudden change in foot symptoms	
Screen for joint surgery	History of joint operations	
Foot pain characteristics	Side of pain	
	Comparative severity of bilateral symptoms	
	Duration	Within 12 months, 1-5 years, 5-10 years, 10+ years (for each foot)
	Preceding accident/injury	Yes/no
	Foot pain/aching/discomfort in last month	Yes/no
Foot pain quality	Short-form McGill Pain Questionnaire [47]	15 sensory and affective descriptors
Sleep disturbance	Self-report	Yes/no
Sensory disturbance	Self-reported tingling/numbness/pins and needles	Yes/no (for each foot)
Causal attribution	What do you think has caused the problem with your foot/feet?	Recorded verbatim
Diagnostic attribution	What do you think is the matter with your foot/feet now?	Recorded verbatim
Foot surgery	Details of any foot surgery	Nature of surgery Right/left < 1 year, 1- < 5 years, 5- < 10 years, 10+ years ago
Foot/ankle injury	Details of foot/ankle injury	Sprain, fracture, other Right/left; forefoot, mid-foot, heel, ankle < 1 year, 1- < 5 years, 5- < 10 years, 10+ years ago
Planned treatment	Are you waiting for any appointments or treatments for this foot or ankle problem?	Yes/no (free text comments for yes)
Importance of health problems	What would you consider to be your two most important health problems at the moment? *[Includes foot problem]*	Recorded verbatim
		

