**Physical examination**		
Screen for clinical "red flags"	Acutely, swollen, hot, painful feet or hands	Yes/no (free text for comments)
Observation	Skin lesions	Bunionette, hyperkeratotic lesions, ulcers (plantar and dorsal aspect)
Toe deformity	MTPJ and interphalangeal joint hyperextension Mallet toe, hammer toe, claw toe, retracted toe	Present/absent (great toe) Present/absent (lesser toes)
Palpation	Mid-foot bony exostosis Plantar fascia tenderness	Present/absent Present/absent (insertion and mid-arch)
Foot posture	Foot Posture Index [50]	Six-criterion scoring system
	Navicular Height [49]	Millimetres
	Foot Length [51]	Millimetres
	Arch index [48,49]	Weightbearing footprint. Length of footprint excluding toes is divided into equal thirds. Arch index = area of middle third divided by area of entire footprint
Range of movement (foot/ankle)	Ankle dorsiflexion (with knee flexed and extended) [53]	Degrees
	Subtalar inversion [52]	Degrees
	Subtalar eversion [52]	Degrees
	1^st ^MTP joint dorsiflexion [54]	Degrees
Knee valgus/varus deformity	Intercondylar distance	Centimetres
	Intermalleolar distance	Centimetres
Anthropometric measurements	Height	Metres
	Weight	Kilograms
Lower limb physical function	Short physical performance battery (SPPB) [57]	Standing balance test, timed repeated chair stand test, 4-metre gait speed test
Hand osteoarthritis	Deformity, enlargement, swelling, nodes [55]	Observation and palpation: swelling (MCPJ), nodes (PIPJ and DIPJ), deformity and enlargement (1^st ^CMCJ, PIPJ and DIPJ)
Hand function	Power grip strength (Jamar dynanometer) [56]	Pounds
	Pinch grip strength (B&L pinch gauge) [56]	Pounds
		

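### A foot ulcer without acute signs is recorded at the research clinic, but the stated communication rule gives it no route to the participant or the General Practice

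*Protocol article*

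**What the plan says.** All references are to the protocol article.

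- **What is recorded.** In Table 2, under physical examination, the skin-lesion row reads "Bunionette, hyperkeratotic lesions, ulcers (plantar and dorsal aspect". The text on the clinical interview and physical examination confirms that skin lesions on both feet are assessed.
- **The communication rule.** The section on communication with the general practice states: "Assessment findings will be communicated to participants and their General Practice only in specific circumstances". Four circumstances follow.
- **The one clinical circumstance.** Mandatory notification of clinical red flags concerns potentially serious pathology that needs urgent attention. It opens its list with "These are: recent trauma to the feet or hands that may have resulted in significant tissue damage" and adds recent sudden worsening of symptoms and acutely hot, swollen, painful feet or hands. A finding leads to an immediate fax, same-day medical attention and a confirming letter.
- **The three x-ray circumstances.** These are mandatory notification of radiographic red flags, discretionary notification of other x-ray abnormality, and an x-ray report at the GP's request. On the discretionary route the article says "the General Practice will be notified of other significant radiographic abnormality (e.g. previous fracture, inflammatory arthropathy".
- **General advice.** The interview and examination section says "Discussion between Research Assessors and participants about diagnosis and/or appropriate management will be discouraged" and also "Participants will be advised to discuss clinical queries with their General Practitioner".

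**The concern.** The study directs a trained podiatrist or physiotherapist to look for ulcers and write down what is found. It then states a rule under which that finding may be passed on only in listed circumstances, and a non-acute ulcer fits none of them. The rule restricts communication to the participant as well as to the practice.

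What is at stake is participant safety. If the article is followed as written, the study can hold a record of an ulcer that nobody responsible for the participant's care has been told about. Any action would then depend on the participant noticing the ulcer and raising it with the GP.

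The case can arise in this population. Attenders are adults aged 50 and over with foot pain in the past year. The survey asks about diabetes, poor circulation and claudication, and the interview asks about numbness and tingling. None of these is a stated exclusion.

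**Working it through.** There is no figure in the plan to reproduce and no formula applies. The check compares the recorded finding with each stated route.

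1. **Is an ulcer a recorded finding?** Yes, on both the plantar and the dorsal aspect (Table 2, physical examination).

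2. **Is it screened as a red flag?** Table 2 has two red-flag items at interview, "Recent significant foot or hand injury Recent sudden change in foot symptoms", and one at examination, "Acutely, swollen, hot, painful feet or hands". That makes 2 + 1 = 3 items, of which 0 name an ulcer. Ulcers sit in the separate skin-lesion row.

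3. **Does any listed circumstance cover it?** Take an ulcer with no recent trauma, no sudden worsening, no acutely hot, swollen, painful foot and no x-ray abnormality:
   - Clinical red flags: 3 triggers, 0 met.
   - Radiographic red flags: require an x-ray finding, so not met.
   - Discretionary notification: requires an x-ray abnormality, so not met.
   - Report on request: started by the GP and limited to the x-ray report, so it does not carry a skin finding.

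   Result: 0 of 4 circumstances apply.

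4. **Which ulcers are already covered?** An ulcer accompanied by any of the three clinical triggers goes through the urgent pathway. An associated x-ray abnormality, such as reported infection, goes through a radiographic route. The gap is what remains.

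5. **Does the general advice close the gap?** No. It directs participants to their GP with queries they already have. It does not have the assessor disclose the ulcer or the study inform the practice.

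6. **Is the list open to additions?** As worded, no. The communication rule says findings are passed on only in the listed circumstances, and the clinical triggers are given as a complete list rather than as examples.

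7. **How many participants?** The document does not say. The 506 in the sample size section is the recruitment target for Phase 2, not a count of people with ulcers. No ulcer prevalence is given, so an expected number cannot be derived.

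**The case against.** The strongest reply is that the red-flag list does its own job. It covers pathology needing urgent attention, and the remaining ulcers are those without the article's own markers of urgency, so leaving them off that list is consistent. This stands. A reader might infer that ulcers should simply be added as a fourth red flag, but that would send every ulcer into an immediate-fax, same-day pathway, and the document gives no ground for that. What does not follow is that non-urgent findings need no route at all. The article itself provides one for non-urgent x-ray abnormalities.

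Second, the article condenses fuller documents. The Assessor Manual is not shown and may tell assessors what to do with an ulcer. This lowers confidence about practice in the clinic but does not remove the stated restriction: a further route in the manual would conflict with the article's wording.

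Third, there are partial safeguards. Discussion is discouraged, not forbidden, so it would be wrong to infer that assessors are barred from speaking. The interview asks whether treatment or appointments are awaited, and some ulcers will already be under care. Many will be visible to the participant, though a plantar one may not be. All of this narrows the group without emptying it.

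Fourth, the comparison with a previous fracture should not be pressed far. That route is discretionary, and participants cannot see their own x-rays.

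**Conclusion.** The point holds as a minor one. By the article's stated rule, a recorded foot ulcer without trauma, sudden worsening, acute signs or an x-ray abnormality has no listed route to the participant or the General Practice: 0 of the 4 circumstances cover it. Only ulcers not already under care are materially affected. Their number is unknown and probably small.

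A reader might infer that ulcers in general go unreported, or that many participants are at risk. The document supports neither. Ulcers with a listed trigger are covered, and there is no basis for a count. Nor is there any effect on the sample size, the power or any planned estimate.

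The conclusion rests on reading the communication rule as closed, which is how it is worded, and on the judgement that an open foot ulcer merits telling the participant and the GP. It makes no claim about what the Assessor Manual contains.

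**What to change.** Add a separate, non-urgent clinical circumstance to the section on communication with the general practice, parallel to the discretionary route for x-ray abnormalities:

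- The assessor tells the participant about any foot ulcer seen that is not already under care, and a routine letter goes to the General Practice.
- The fax and same-day arrangements remain for ulcers with acute signs.
- The new circumstance is included in the explanation given at the start of the clinic and in the Assessor Manual.
- Each letter is logged with its date, so that consultations it may have prompted can be identified in the Phase 3 record review.

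The cost is one added paragraph, a line in the clinic explanation and the manual, a question on whether the ulcer is already being treated, and probably a few letters. No new examination or staff are needed, because ulcers are already recorded.

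There is a small downside. A few letters may prompt consultations of the kind that aims (iv) to (vi) study, as the existing notifications already can. Logging makes these identifiable but does not remove the effect.
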